## Abstract

**Background:**

All patients who undergo surgery for colon cancer are followed up according to the guidelines of the Norwegian Gastrointestinal Cancer Group (NGICG). These guidelines state that the aims of follow-up after surgery are to perform quality assessment, provide support and improve survival. In Norway, most of these patients are followed up in a hospital setting. We describe a multi-centre randomized controlled trial to test whether these patients can be followed up by their general practitioner (GP) without altering quality of life, cost effectiveness and/or the incidence of serious clinical events.

**Methods and Design:**

Patients undergoing surgery for colon cancer with histological grade Dukes's Stage A, B or C and below 75 years of age are eligible for inclusion. They will be randomized after surgery to follow-up at the surgical outpatient clinic (control group) or follow-up by the district GP (intervention group). Both study arms comply with the national NGICG guidelines. The primary endpoints will be quality of life (QoL) (measured by the EORTC QLQ C-30 and the EQ-5D instruments), serious clinical events (SCEs), and costs. The follow-up period will be two years after surgery, and quality of life will be measured every three months. SCEs and costs will be estimated prospectively. The sample size was 170 patients.

**Discussion:**

There is an ongoing debate on the best method of follow-up for patients with CRC. Due to a wide range of follow-up programmes and paucity of randomized trials, it is impossible to draw conclusions about the best combination and frequency of clinic (or family practice) visits, blood tests, endoscopic procedures and radiological examinations that maximize the clinical outcome, quality of life and costs. Most studies on follow-up of CRC patients have been performed in a hospital outpatient setting. We hypothesize that postoperative follow-up of colon cancer patients (according to national guidelines) by GPs will not have any impact on patients' quality of life. Furthermore, we hypothesize that there will be no increase in SCEs and that the incremental cost-effectiveness ratio will improve.

**Trial registration:**

This trial has been registered at ClinicalTrials.gov. The trial registration number is: NCT00572143

## Background

An increasing incidence of colorectal cancer (CRC) has been observed in Norway during the past decades. According to the Cancer Registry of Norway, 2296 new cases of colon cancer were reported in 2006, making the disease among the most common type of cancer in both genders. The incidence in Norway is significantly higher than in the other Nordic countries [1]. The background for this discrepancy is unknown [2]. The overall five-year survival rate in 1993–97 was 56% for males and 60% for females [3]. At the time of diagnosis, about two thirds of patients had undergone resection, but 30–50% of them relapsed and died of the disease [4].

There is an ongoing debate on the best follow-up regimen for patients with CRC [5-7]. A meta-analysis published in 2002, including 1342 patients, demonstrated that intensive follow-up in CRC was associated with an absolute reduction in 5-year all-cause mortality of 10% [8]. Other trials have revealed similar results [9]. Due to the wide range of follow-up programmes employed, it is impossible to draw conclusions on the best combination and frequency of clinic visits, blood tests, endoscopic procedures, and radiological examinations that maximize the clinical outcome. Furthermore, the potential harms and costs of an intensified follow-up programme have not been clarified. The Norwegian Gastrointestinal Cancer Group (NGICG) revised its follow-up guidelines (Table 1) in 2007 [10]. According to these guidelines, most of the follow-up can be done by GPs. The aims of the follow-up programme are to perform quality assessment, provide support and improve survival. Most relapses (80%) of colon cancer are detected within the first three years of follow-up [11]. Based on this knowledge, the regular check-ups are recommended at three- month intervals for the first two years and then every six months. A similar CRC surveillance guideline was presented in 2005 by the American Society of Clinical Oncology (ASCO) [12].

**Table 1 T1:** Follow-up of patients with colon cancer as proposed by the Norwegian Gastrointestinal Cancer Group (NGICG).

**Examination**	**Months postoperative**														
	
	1	3	6	9	12	15	18	21	24	30	36	42	48	54	60
Chest x-ray			X		X		X		X		X		X		X
Ultrasound liver			X		X		X		X		X		X		X
Coloscopy			X										X		
CEA measurement^a^	X	X	X	X	X	X	X	X	X	X	X	X	X	X	X
Clinical examination	X	X	X	X	X	X	X	X	X	X	X	X	X	X	X

This guideline is employed at Norwegian hospitals and will be used in both trial arms.

^a^Only patients with elevated CEA prior to surgery are requested to undergo this test during the follow-up.

During recent years, several critical articles have been published arguing against present follow-up procedures. So far, most studies addressing follow-up of CRC patients have been performed in a hospital setting. According to a recent Cochrane review, further research is needed, focusing on follow-up schedules in either a hospital setting or in general practice [6]. Whereas systematic postoperative surveillance has been extensively studied with regard to cure and survival, the possible benefits in terms of improved palliative care and/or quality of life have been less widely documented.

The purpose of this study is to obtain insight into quality of life among colon cancer patients followed up in a hospital outpatient setting or by their GPs and into the incremental cost-effectiveness ratio from the point of view of health care and of society.

## Methods and Design

### Study design

This trial is a multi-centre randomized controlled study where patients will either be randomized to follow-up at the hospital (control group) or by their GP (intervention group) (Figure 1).

**Figure 1 F1:**
[figure not shown]
Trial Flow Chart

### Participants

#### Patients

Patients are eligible if they undergo surgery for colon cancer with histological grade Dukes's Stage A, B or C. Patients receiving postsurgical adjuvant chemotherapy (Dukes C) are also eligible. We define a colon cancer as a tumour located 15 cm above the anal verge by coloscopy or a tumour at or above the level of the sacral promontory as seen at the time of surgery. Annually, approximately 200 patients with colon cancer undergo surgery in the catchment area of the North Norwegian Hospital Trust (a population of 470,000).

#### Hospitals

There are three hospital trusts and one university hospital (UNN HF) (in total 11 hospital units) located within the North-Norwegian Health Region. Three hospitals (located in the cities of Harstad, Mo, and Bodø) have an annual volume of more than 20 colon cancer procedures; the University Hospital operates on about 110 patients with suspected CRC cancer annually and approximately 60 of them have a colon cancer disclosed. The University Hospital and these three local hospitals consented to participate. All patients who undergo surgery for colon cancer are followed up at the surgical outpatient clinic at each hospital.

#### GPs

In North Norway, 550 GPs refer patients with suspected colon cancer to the local hospitals. They are situated in all communities in North Norway. All GPs were informed by mail about the purpose of the study and invited to participate. None refused to participate.

### Intervention

Patients are randomized to follow-up either by their GP (intervention) or at the surgical outpatient clinic. All patients will receive their first postoperative check-up at the hospital which performed the surgery (baseline, 1 month). A clinical examination will then be performed and information about the histology and the results of the surgery will be provided. If the patient gives informed consent, randomization is performed. Patients randomized to GP follow-up are referred to their GP. This referral contains information about the surgery and any complications, Dukes's staging, guidelines for follow-up and behavioural strategy in the case of a SCE.

#### Guidelines for follow-up

NGICG revised its guidelines in 2007 [10] (Table 1), and the GPs were provided with a guideline form based upon this recommendation. Most relapses of colon cancer are detected within the first three years of follow-up. On the basis of this knowledge, the regular check-ups are performed at three-month intervals for the first two years and then every six months.

All patients with elevated CEA prior to surgery are requested to undergo this test at every postoperative clinical examination. Chest x-ray and ultrasound are performed on a regular basis. Colonoscopy is performed twice during the follow-up period. The follow-up guideline is similar in both arms (Table 1).

#### When recurrence is suspected

All GPs are given written instructions on what to do if recurrence is suspected. A set of serious clinical events (SCEs) is defined as: Colonoscopy verifies recurrence of CRC. Elevated levels of CEA are shown by repeated measurements. Blood in stool is detected by the Hemofec test. Unexplained abdominal pain. Unexplained weight loss of 5 kg during the last three months. Cancer-suspect lesions detected by rectal examination. Lymphandenopathy. Metastasis-suspect lesions shown by chest x-ray or ultrasound of liver. If an SCE occurs, the patient must be referred promptly to hospital.

#### Information to the patient

All patients included in the study are given a folder explaining the purpose of the study. Follow-up guidelines are provided with detailed information concerning the clinical examinations, CEA measurements, x-ray/ultrasound procedures and colonoscopy.

#### QOL questionnaires

The EQ-5D and EORTC-QLQ C30 questionnaires for the two-year follow-up period (at 1, 3, 6, 9, 12, 15, 18, 21, 24 month follow-up) are given to the patient at baseline examination.

Economic evaluation questionnaire: A questionnaire has been developed to enable calculation of costs related to patient examinations. This questionnaire is incorporated in the QOL questionnaire, and patients are requested to fill out the questionnaire at 1, 3 6, 9, 12, 15, 18, 21 and 24 months postoperatively. The cost elements will include patient- and family-related costs due to outpatient visits, GP visits, laboratory tests, radiographs/ultrasound, examinations due to suspected relapse, treatment of relapse, travelling, production losses, co-payments and other patient expenses.

### Control arm

Patients in the control group consist of patients randomized to regular follow-up at the hospital's surgical outpatient clinic. All these patients are followed up according to the NGICG guidelines. This follow-up is performed by consultants or internship doctors in digestive surgery.

### Objectives

#### Primary objective

We aim to compare quality of life and costs of follow-up among patients followed up by their local GP or at the surgical outpatient clinic. We hypothesize that patients followed up by their GP will experience similar or higher scores on quality of life measures and lower costs during follow-up.

#### Secondary objective

We aim to test whether the incidence of SCEs will be similar for patients followed up by their GP and patients in the control group. We hypothesize that patients followed up by their GP will not have an increase in time to detection or in the frequency of SCEs.

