### Sample size

Sample size calculations are according to Campbell's guidelines [15]

Alpha and beta were set at 0.05 and 0.2 respectively and tests were two-sided. We hypothesize that patients followed up by their GP will have a minor to moderate increase in the Global QoL scores (EORTOC-QLQ C30). This moderate effect size equals an increase of 10 units on the Global QOL [16]. Patients with colon cancer (local disease) show a standard deviation of approximately 20 (global QOL) [16]. Allowing for a dropout rate of 20%, to detect this difference with confidence we required a total sample size of 170 patients. Sample size calculations based upon EQ-5D showed similar results [17].

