### Analysis

We will use the intention-to-treat principle when analysing data. Furthermore, we will employ Fayers guidelines to handle missing data [18]. Treatment arms will be compared with respect to potential covariates using continuous and categorical univariable analyses. These will include variables relating to patients (age, sex, comorbidities, cost), treatment (surgical resection, surgical complications, adjuvant therapy), tumour (Dukes's Stage), hospital surgical outpatient clinic (cost, patient satisfaction, QoL), GP practice (cost, patient satisfaction, QoL). The cost elements will include costs related to outpatient visits, GP visits, laboratory tests, radiographs/ultrasound, and examinations due to suspected relapse, treatment of relapse, travelling/transportation, production losses, co-payments and other patient expenses. The net costs and outcomes of the two treatment options will be compared and presented as cost-effectiveness ratios. If the trial reveals no difference in health outcomes or quality of life for the patients, a cost-minimization analysis will be carried out. If we find a difference in quality of life or overall survival rates between the two groups, we will use a cost-utility approach. The economic evaluation will have a societal and health care perspective.

The method of analysis, including adjusting for covariates will comply with the CONSORT statement [19]. The results will be expressed as odds ratios for binary outcomes, hazard ratios for time- to-event outcomes or mean differences for continuous outcomes with corresponding standard errors, 95% confidence intervals, and associated p-values. P-values will be reported to three decimal places with p-values less than 0.001 reported as p < 0.001. For all tests we will use alpha = 0.05 level of significance.

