The geography of Norway makes the costs of travelling a significant burden. In North Norway in particular, the population is scattered throughout a large geographic area, making the cost of travel to a specialist examination considerable. The specialists are mainly located in a few main cities. New regulations requiring each hospital to cover travel expenses have resulted in a stronger focus on these costs in recent years. At present, 5% of the total budget of the Regional Health Authority of North Norway is spent on travelling/transportation. The cost of travelling was earlier funded by the Norwegian Insurance Administration. If a follow-up programme (i.e. clinical examination and medical history) can be run by the patient's GP, there are obvious reasons to believe that the total costs of such a programme could be reduced.

Whereas there is evidence of survival gain related to intensive follow-up programmes, the burden of cost to the health care service is considerable [26-28]. Renehan et al. published a study in 2004 arguing that intensive follow-up after curative resection for colorectal cancer is economically justified and should be standard practice [29]. However, a Danish study concludes the opposite, stating that follow-up after colorectal cancer surgery is not cost-effective compared to several other procedures, including screening for CRC [21]. The cost-effectiveness of the Norwegian guidelines was documented cost-effective in a prior study when applied in a model-based study implementing data from the literature. The basic cost of the NGICG recommended programme was GBP£ 1,232 per patient. Including extended investigation due to suspected relapse in 45% of cases, the figure rose to £ 1,943 per patient [30]. However, Korner et al [23] argue against this study. The total programme cost in this study was Euro € 228,117 (US 280,994 dollars), translating into € 20,530 (US 25,289 dollars) for one surviving patient after salvage surgery. This cost is less than the one calculated by Norum, but the costs are calculated at different times and in different settings, making a direct comparison useless. Costs are hard to compare with publications from other countries because of different reimbursement policies. Finally, they [23] argue whether the continuing implementation of such a program and costs are justified should be further debated.

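### The claim that SCEs do not worsen under GP follow-up rests on a 0.05 test with no stated tolerable limit, in a trial sized on quality of life; a moderate worsening would usually be missed.

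*Protocol article*

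**What the plan says.** The Secondary objective section states "We aim to test whether the incidence of SCEs will be similar for patients followed up by their GP" as in the control group, and adds "We hypothesize that patients followed up by their GP will not have an increase in time to detection or in the frequency of SCEs". The Discussion part of the abstract repeats it: "we hypothesize that there will be no increase in SCEs". The Background part of the abstract likewise asks whether GP follow-up leaves SCE incidence unaltered.

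The Analysis section provides odds ratios, hazard ratios or mean differences with 95% confidence intervals and p-values, and closes with "For all tests we will use alpha = 0.05 level of significance". It gives no rule for concluding that two arms are alike. It and the Economic analysis section both move to cost-minimization if the trial shows no difference in health outcomes or quality of life.

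The Sample size section says "Alpha and beta were set at 0.05 and 0.2 respectively and tests were two-sided". It takes a 10-unit gain on Global QoL, an SD of about 20 and 20% dropout, and concludes "to detect this difference with confidence we required a total sample size of 170 patients". It adds that an EQ-5D calculation gave a similar answer. It gives no SCE rate, event count or precision.

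**The concern.** A hypothesis of sameness cannot be supported by failing to reject a test of difference. It needs a largest acceptable difference and an interval that excludes it. The article states the first kind of hypothesis and supplies only the second kind of test.

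SCEs are the outcome that would show whether recurrence is picked up as often and as early by GPs. If non-significance is read as no increase, the trial could report a safety result that it has not shown. The cost-minimization step makes this more than a matter of phrasing, because that analysis treats outcomes as equal. The trigger does not name SCEs, but they are the natural content of health outcomes in this trial.

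**Working it through.** **The plan's own figure.** With a difference of 10, SD 20, two-sided 0.05 and 80% power, the normal approximation gives 63 per arm, so 126 in total and 126/0.8 = 158 after dropout. The t-test version gives 64 per arm, 128 and 160. The stated 170 is slightly larger, which errs on the safe side: 170 × 0.8 = 136, or 68 per arm, gives 83% power for Global QoL. Size is not the problem for quality of life. The question is what 170 gives for SCEs.

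**Inputs.**
- 85 per arm: 170 split 1:1. The ratio is not stated, so 1:1 is assumed. No dropout is taken, since SCEs come from chart review at 24 months.
- Control-arm 24-month SCE rate p: not given, so 15-45% is assumed. The nearest figures are the Discussion's "Including extended investigation due to suspected relapse in 45% of cases" and the Background's 30-50% relapse and death after resection. Neither is a 24-month SCE rate.
- Two-sided 0.05, z = 1.96.

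**Rise in incidence.** Power = Φ(d / √[(p(1−p) + q(1−q))/85] − 1.96), with q = p + d.
- d = 0.10, p = 0.15: SE = √[(0.1275 + 0.1875)/85] = 0.0609; 0.10/0.0609 − 1.96 = −0.32; power 38%.
- d = 0.10, p = 0.45: SE = √[(0.2475 + 0.2475)/85] = 0.0763; 0.10/0.0763 − 1.96 = −0.65; power 26%.

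| True rise | p = 15% | 20% | 30% | 45% |
|---|---|---|---|---|
| 10 points | 38% | 33% | 28% | 26% |
| 15 points | 66% | 60% | 53% | 51% |
| 20 points | 87% | 83% | 78% | 76% |

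**Hazard ratio.** Events E = 85(p + q), with q = 1 − (1 − p)^HR; power = Φ(√E × |ln HR|/2 − 1.96).
- HR 1.5: E = 31.1 at 15% gives 20%; E = 88.6 at 45% gives 48%.
- HR 2.0: E = 36.3 at 15% gives 55%; E = 97.5 at 45% gives 93%.

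**Detection delay.** Assume a constant hazard λ = −ln(1 − p)/24, with every GP-arm detection shifted by s months and cut off at 24. Then q = 1 − exp(−λ(24 − s)). Person-time is p/λ in the control arm and s + q/λ in the GP arm. HR is the ratio of events per person-time, and power is as above.

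| Delay | p | GP-arm rate q | HR | Events | Power |
|---|---|---|---|---|---|
| 3 months | 15% | 13.3% | 0.87 | 24.0 | 5% |
| 3 months | 45% | 40.7% | 0.85 | 72.9 | 11% |
| 6 months | 15% | 11.5% | 0.74 | 22.5 | 11% |
| 6 months | 45% | 36.1% | 0.71 | 69.0 | 30% |

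The q column shows a second difficulty. Late detection lowers the 24-month count, so an arm that detects late can meet a rule of no increase in frequency.

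**Precision with truly equal arms.** The half-width of the 95% interval for the incidence difference is 1.96 × √[2p(1−p)/85], which is 10.7 points at 15% and 15.0 points at 45%. For the hazard ratio, the upper limit is exp(1.96 × 2/√(170p)), which is 2.17 at 15% and 1.57 at 45%.

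**What a firm claim would need (illustrative only, not proposed limits).** Take equal true rates, one-sided 0.025, 80% power and 20% dropout. Excluding a 10-point rise needs 630 patients at a 20% rate and 973 at 45%. Excluding a hazard ratio of 1.5 needs 191 events, more than the number of patients.

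**The case against.** The strongest objections are these.

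- *Large rises are not usually missed.* This stands. A 20-point rise is found in 76-87% of trials and a doubled hazard in 55-93%, while a 15-point rise is close to a coin toss at the higher rates. A reader might infer that almost any harm would pass unnoticed; the arithmetic does not support that.
- *The plan promises 95% confidence intervals.* This stands too. It would be wrong to say that p > 0.05 is the only reading available, since the intervals would show the imprecision. But no limit is set to read them against, and the cost-minimization step acts on a finding of no difference.
- *The trial was not sized on Global QoL alone.* Correct: an EQ-5D calculation is also cited. Neither calculation concerns SCEs.
- *A secondary outcome need not be powered, and margins may sit in an analysis plan that is not shown.* Fair as far as it goes. SCEs are secondary in the Objectives and Outcome sections, although the abstract lists them among the primary endpoints. The point does not depend on an omitted detail: the article itself pairs a sameness hypothesis with a difference test and an action on no difference.
- *The rates and the delay model are assumptions.* True. The SCE composite includes symptoms such as abdominal pain, so rates above 45% are possible; at 60%, power for HR 1.5 would be about 58%. A uniform delay is a simplification, since both arms follow the same schedule, and 3 months is a single check-up interval.

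**Conclusion.** The concern holds in a limited form. The SCE aim is one of similarity or no increase, the only stated criterion is a 0.05 test without a tolerable limit, and a finding of no difference can move the economic analysis to cost-minimization. The sample size was set on quality of life and says nothing about SCEs.

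With 85 per arm and an assumed 24-month rate of 15-45%, a true 10-point rise would be missed in 62-74% of trials, a hazard ratio of 1.5 in 52-80%, a 3-month delay in 89-95% and a 6-month delay in 70-89%. The documents do not support saying that a large rise would usually be missed, or that the investigators have committed themselves to declaring similarity from a non-significant p-value. They leave that reading open and provide nothing that prevents it. The percentages depend on the assumed rate, 1:1 allocation and, for delay, a constant hazard with a uniform shift. The mismatch between hypothesis and criterion depends on none of these.

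**What to change.** 1. **Secondary objective and Analysis.** Report SCE incidence and time to detection as estimates with the 95% confidence intervals already planned. State that p > 0.05 is not evidence of similarity. Claim similarity or no increase only if the interval excludes a limit stated and justified in advance by the trial team; otherwise report the result as inconclusive.
2. **Incidence and delay together.** Judge the two jointly and read incidence in both directions, because fewer SCEs by 24 months may reflect later detection.
3. **Economic analysis and Analysis.** Do not let a non-significant SCE result alone trigger cost-minimization. Carry the SCE uncertainty into the economic evaluation.
4. **Sample size.** State that 170 was set for quality of life, and give the SCE precision it yields: a 95% interval half-width of about 11-15 points for the incidence difference under the assumed rates.
5. **Abstract.** Word the SCE aim as estimation unless the rule in item 1 is adopted.

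The cost is wording in the protocol and analysis plan, with no extra patients or data. The price is a less favourable SCE conclusion, which will probably be inconclusive.

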### Secondary outcome measures

#### Serious clinical events (SCEs)

Time to detection of recurrences and serious clinical events (SCEs) defined as: Colonoscopy-verified recurrence of cancer disease. Increase in CEA measurements shown by repeated measurements. Blood in stool detected by the Hemofec test. Unexplained abdominal pain. Unexplained weight loss of 5 kg during the last three months. Cancer-suspect lesions detected in rectal examination. Lymphandenopathy. Metastatic suspect lesions shown by chest x-ray or ultrasound of liver.

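### Similar SCE incidence is sought without a margin, on a detection-dependent outcome whose count falls if the GP arm detects less

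*Protocol article*

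**What the plan says.** The Secondary objective section aims to test whether SCE incidence will be similar and continues: "We hypothesize that patients followed up by their GP will not have an increase in time to detection or in the frequency of SCEs". The abstract's Discussion carries forward the frequency half: "we hypothesize that there will be no increase in SCEs".

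The outcome is headed "Time to detection of recurrences and serious clinical events (SCEs) defined as", followed by a list: colonoscopy-verified recurrence, repeated CEA rise, blood in stool, unexplained abdominal pain, 5 kg weight loss, suspect rectal lesion, lymphadenopathy, and suspect lesions on chest x-ray or liver ultrasound. The section on suspected recurrence uses the same list to trigger referral to hospital. Data gathering registers SCEs by hospital chart review at 24 months after surgery.

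The Analysis section fixes the effect measures ("The results will be expressed as odds ratios for binary outcomes, hazard ratios for" time-to-event outcomes), promises 95% confidence intervals and p-values, and adds: "For all tests we will use alpha = 0.05 level of significance". The Sample size section says "Alpha and beta were set at 0.05 and 0.2 respectively and tests were two-sided" and rests on global quality of life: "This moderate effect size equals an increase of 10 units on the Global QOL". It mentions no SCE rate, margin or power. The Economic analysis and Analysis sections both make a finding of no difference in health outcomes or quality of life the trigger for a cost-minimization analysis.

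**The concern.** Two matters come together.

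The first is direction. An increase in frequency would show as an odds ratio or hazard ratio above 1. An increase in time to detection would show as a hazard ratio below 1. Most listed SCEs exist in the data only once someone has looked, found and referred. An arm that misses or delays findings therefore shows fewer SCEs by 24 months. On the frequency half that is no increase; on the other half it is a failure. The article does not say which side of 1 is unfavourable, or how the two halves combine.

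The second is the absence of a margin. An aim of similarity needs either a margin or a statement that the comparison is estimation only. Here there are an alpha of 0.05, a sample sized on something else, and a consequence attached to finding no difference.

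At stake is the safety statement that would support moving follow-up to GPs, and the choice of a cost-minimization analysis.

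**Working it through.** **The plan's own figure.** The only sample size is for global quality of life: difference 10, SD 20, two-sided 0.05, power 0.80. Per arm, n = 2 × (1.96 + 0.8416)² × (20/10)² = 62.8, so 63; total 126; 126/0.8 = 158 after 20% dropout. The t-test version gives 64 per arm, hence 160. The stated 170 is somewhat larger and so on the safe side for quality of life (about 83% power with 68 per arm). It says nothing about SCEs.

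**Inputs for SCEs.** Total 170 (Sample size). Allocation of 85 per arm is assumed, as the ratio is not stated. No SCE rate is given, so 20% to 45% by 24 months is assumed. The upper end borrows the 45% extended investigation for suspected relapse that the main Discussion section quotes from a model-based study. Randomization is at 1 month, leaving 23 months.

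**Precision with no observed difference and no dropout.** Upper 95% limit for the hazard ratio = exp(1.96 × 2/√events). Risk-difference half-width = 1.96 × √(2p(1−p)/85).

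| Rate p | Events | Upper HR limit | Half-width |
|---|---|---|---|
| 20% | 34 | 1.96 | 12.0 points |
| 30% | 51 | 1.73 | 13.8 points |
| 45% | about 76 | 1.57 | 15.0 points |

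With 68 per arm the half-widths become 13.4, 15.4 and 16.7 points.

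**Direction.** Take a control rate of 30% by 23 months with exponential times and equal true rates.
- GP arm misses 30% of events: observed rate 0.30 × 0.70 = 0.21; OR = (0.21/0.79)/(0.30/0.70) = 0.62.
- Detection 3 months late: 1 − 0.7^(20/23) = 0.267; OR = 0.85.
- Detection 6 months late: 1 − 0.7^(17/23) = 0.232; OR = 0.70.

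A simulation with 85 per arm and 800 runs per scenario agrees: median OR 0.61, 0.84 and 0.69; median HR 0.66, 0.85 and 0.69. A significant hazard ratio above 1 appeared in at most 0.5% of runs.

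**What a non-significant test would mean.** In the same simulation, with 30% of events missed, the two-sided Cox test was non-significant in 83%, 73% and 57% of runs at control rates of 20%, 30% and 45%. With a 3-month delay it was non-significant in about 90%. With a 6-month delay the figures were 80% (rate 30%) and 69% (rate 45%). The formula for two proportions gives power of 18%, 27% and 44% to see a 30% loss of detection.

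**Scale of a margin-based claim, for illustration.** n per arm = (1.96 + 0.8416)² × 2p(1−p)/margin². A 10-point margin needs 252, 330 or 389 per arm at rates of 20%, 30% or 45%; a 15-point margin needs 112, 147 or 173. The trial has 85.

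**The case against.** The hypothesis has two halves, and the time-to-detection half does guard against delay: a GP arm that detects late fails it. The aim is similarity, which can be read in both directions. No sentence calls fewer SCEs favourable or equates p>0.05 with safety, and 95% confidence intervals are already promised. SCEs are secondary in the Objectives and Outcome sections, and a secondary outcome does not normally need its own power calculation. (The abstract's Methods lists SCEs among the primary endpoints, which weakens that last defence.)

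Much of this stands, and it rules out stronger readings:
- A reader might infer that missed relapse would be scored as a success. The text does not say so. Only the frequency half, read alone, or a non-significant result permits it.
- A reader might infer one pooled hazard ratio in which a delay and an excess of events cancel. The Analysis section is a generic list of measures, and the outcome wording can be read as naming recurrence apart from SCEs. With random allocation and the same schedule in both arms, the documents give no reason to expect an offsetting excess.
- A reader might infer that non-specific signs dominate the list. No figure supports this.
- A reader might want one fixed hazard ratio limit written into the plan. That would rest on an assumed rate.

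The objection does not remove the two stated facts: similarity is sought without a margin, and the frequency half points the wrong way for a detection-dependent outcome. Both lie in the hypothesis as published and are not detail that would wait for an analysis plan.

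**Conclusion.** The point holds in a limited form. The secondary objective seeks similarity with no margin, on events that are largely detection findings. Poorer GP detection would lower SCE frequency and so meet the wording on no increase in SCEs, while conflicting with the time-to-detection half of the same sentence. A non-significant test at 0.05 in a trial sized on quality of life cannot establish similarity. It also should not by itself serve as the finding of no difference that leads to cost-minimization.

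An observed hazard ratio of 1 would leave an upper 95% limit of about 2.0 to 1.6, and a risk-difference half-width of about 12 to 15 points. This assumes 1:1 allocation, no dropout and event rates of 20% to 45%, none of which the article states. The sizes of the simulated misses and delays are likewise illustrations, not predictions about GP care.

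**What to change.** Amend the Secondary objective, the SCE outcome definition and the Analysis section as follows.

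1. Report hospital-confirmed recurrence by 24 months separately from the symptom and sign triggers. For recurrence, give the risk difference and the time to detection as a hazard ratio from randomization, in all randomized patients, with 95% confidence intervals. Present the triggers descriptively.
2. State that a lower SCE count or a hazard ratio below 1 in the GP arm may reflect missed or late detection and is not in itself favourable, so that departures in either direction are of concern. This is needed for confirmed recurrence too, since its count also falls when relapses are missed.
3. Replace similarity and no increase, as conclusions of a test, with the two-sided 95% confidence interval and a statement of the differences it excludes. Say that p>0.05 is not evidence of safety, and not by itself the trigger for cost-minimization.

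Any interval from first recorded SCE to confirmation should be descriptive only. It conditions on an event after randomization, misses delay before the first recorded sign, and may need dates held in GP notes instead of hospital charts.

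The cost is mainly wording, with recurrence taken from the chart review already planned and no more patients. The downside is a weaker safety claim than the abstract promises.
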